## Abstract

**Background:**

Major depression and type 2 diabetes often co-occur. Novel treatment strategies for depression in type 2 diabetes patients are warranted, as depression in type 2 diabetes patients is associated with poor prognosis and treatment results. Major depression and concurrent sleep disorders have been related to disturbances of the biological clock. The biological clock is also involved in regulation of glucose metabolism by modulating peripheral insulin sensitivity. Light therapy has been shown to be an effective antidepressant that ‘resets’ the biological clock. We here describe the protocol of a study that evaluates the hypothesis that light therapy improves mood as well as insulin sensitivity in patients with a major depressive episode and type 2 diabetes.

**Methods/design:**

This study is a randomised, double-blind, parallel-arm trial in 98 participants with type 2 diabetes and a major depressive episode, according to DSM-IV criteria. We will assess whether light therapy improves depressive symptoms and insulin sensitivity, our primary outcome measures, and additionally investigate whether these effects are mediated by restoration of the circadian rhythmicity, as measured by sleep and hypothalamic-pituitary-adrenal axis activity. Participants will be randomly allocated to a bright white-yellowish light condition or dim green light condition. Participants will undergo light therapy for half an hour every morning for 4 weeks at home. At several time points, namely before the start of light therapy, during light therapy, after completion of 4 weeks of light therapy and after 4 weeks follow-up, several psychometrical, psychophysiological and glucometabolic measures will be performed.

**Discussion:**

If light therapy effectively improves mood and insulin sensitivity in type 2 diabetes patients with a major depressive episode, light therapy may be a valuable patient friendly addition to the currently available treatment strategies. Additionally, if our data support the role of restoration of circadian rhythmicity, such an observation may guide further development of chronobiological treatment strategies in this patient population.

**Trial registration:**

The Netherlands Trial Register (NTR) NTR4942. Registered 13 January 2015.

## Background

Major depression is a mood state characterised by depressed mood and loss of interest or pleasure for at least 2 weeks, together with several other symptoms, such as loss of energy, diminished ability to concentrate, changes in appetite or physical activity and sleep disturbances. Up to 20 % of the type 2 diabetes (T2D) patients suffer from major depression [1], where depression appears to be more persistent and recurrent [2–4] and has adverse effects on health behaviour and treatment adherence [5, 6]. Consequently, depression in T2D patients is associated with an increased risk for diabetes complications and mortality [7–16], as well as an economic burden to society [17, 18]. Hence, adequate treatment of depression in T2D patients is required.

Major depression in T2D patients can be treated by psychotherapy or antidepressant drugs. Meta-analytic evidence has shown that antidepressant treatments, both psychological and pharmacological, are only moderately effective in the reduction of depressive symptoms in T2D patients [19, 20]. Glycaemic improvements from anti-depressant therapies have been very modest [20] and some antidepressant drugs have even shown negative metabolic effects, such as weight gain [21] and glucose dysregulation [22]. There clearly is a need for more efficacious treatment strategies of major depression in T2D patients, which improve both psychiatric symptoms and glycaemic control [23].

Light therapy has been shown to be a patient friendly, non-pharmacological antidepressant, which has an early onset of action and a mild adverse-effect profile [24]. Light therapy has been proven successful in patient groups that are traditionally difficult to treat, such as patients with chronic depression and postpartum depression [25–27], and may therefore be effective in the treatment of major depression in T2D patients. Restoration of the circadian rhythmicity, which is often disrupted in depression, has been assumed to be the mechanism of action of light therapy [28]. The biological mechanism behind this chronobiological effect is that light induces the specialised light sensitive retinal ganglion cells to release glutamate in the suprachiasmatic nucleus (SCN) of the brain, which is often called the ‘biological clock’ [29]. The SCN is involved in the regulation of melatonin release, activation of the hypothalamic-pituitary-adrenal (HPA) axis as well as regulation of sleep-wake patterns. A recent clinical study in elderly patients with non-seasonal depression showed that light therapy improved mood, increased upslope evening melatonin levels, attenuated cortisol release and enhanced sleep efficiency [30]. The SCN is also involved in regulation of glucose metabolism [31], which suggests that light therapy may affect glucose metabolism. Two case reports on the effect of light therapy in patients with seasonal depression and insulin dependent diabetes support the idea of effects of light therapy on glucose metabolism [32, 33].

Sleep disturbances, which are indicative of disturbed circadian rhythmicity, often co-occur with major depression [34] and have been associated with hyperglycaemia and increased rates of incident diabetes [35]. In patients with T2D, sleep disorders are associated with a 23 % higher fasting glucose level, a 48 % increment in fasting insulin levels and a decreased insulin sensitivity as indicated by a 82 % increase in homeostatic model assessment of insulin resistance (HOMA-IR) [36, 37]. Two studies using a hyperinsulinaemic-euglycaemic clamp procedure, which is considered the gold standard for the quantification of whole-body insulin sensitivity, observed strong effects of one single night of sleep restriction on insulin sensitivity in healthy volunteers [38] and in patients with type 1 diabetes [39]. Whether the reversed situation, improved insulin sensitivity, can be reached after restoration of the circadian rhythmicity in patients with sleep disturbances has, to the best of our knowledge, not been tested.

We believe that light therapy may be a promising treatment option for patients with major depression and T2D, as light therapy may result in concurrent improvements in depressive symptoms and insulin sensitivity through restoration of the circadian rhythmicity (Fig. 1). To substantiate this theory, we aim to perform a randomised, double-blind, parallel-arm trial that investigates the following hypotheses:Light therapy improves depressive symptoms in patients with a major depressive episode and T2D.Light therapy improves insulin sensitivity in patients with a major depressive episode and T2D.Effects of light therapy on depressive symptoms and insulin sensitivity are mediated by restoration of the circadian rhythmicity, as measured by the sleep-wake pattern and HPA axis activity.

**Fig. 1 Fig1:**
[figure not shown]
Research hypothesis. Schematic overview of the research hypothesis. **a** Schematic overview of the relationship between the biological clock, depressive symptoms and insulin sensitivity in patients with major depression and type 2 diabetes. **b** Schematic overview of the hypothesised effect of light therapy on the biological clock, depressive symptoms and insulin sensitivity in patients with major depression and type 2 diabetes

If light therapy proves to be an effective antidepressant in T2D patients and improves insulin sensitivity, light therapy may be a valuable addition to the currently available treatment options for major depression in T2D patients, assuming that improvements in insulin sensitivity may ultimately lead to improvements in glycaemic control.

## Methods/design

### Design

This study entails a randomised, double-blind, parallel-arm trial, consisting of a run-in period of at least 1 week to allow for study effects, a four-week intervention period and a four-week follow-up period. Assessments of primary and secondary outcome measures, as well as mediating factors, will be performed at baseline, during the intervention, after the intervention and after the follow-up period to assess direct and long-term effects of light therapy. The trial methods reporting is consistent with the CONSORT statement [40]. A schematic overview of the trial protocol is provided in Fig. 2.

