### Participants

Participants will be recruited using a number of strategies: (1) Participants of previous research studies of the VU University Medical Centre will be informed about the study; (2) patients will be informed about the study by affiliated health-care-workers; (3) advertisements in local newspapers, folders and posters in waiting rooms of affiliated health-care-institutions; and (4) via our website. In case patients are interested in participation, a screening consisting of three questions will be applied by telephone. Only patients without a history of laser photocoagulation for the treatment of diabetic retinopathy and scoring 2 or more on one or both questions of the Patient Health Questionnaire-2, a screening tool for a major depressive episode [42], will be invited for a screening visit.

Eligibility for participation will be determined during a screening visit, which constitutes a standardised psychiatric interview, as assessed with the Composite International Diagnostic Interview (CIDI) WHO version 2.1 [43], a medical interview on disease history and medication, physical and blood examination, visual acuity test and fundus photography.

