#### Inclusion criteria

Participants will be included when (1) 18 years or older; (2) having a documented physician-based diagnosis of T2D; and (3) having a major depressive episode according to DSM-IV criteria.

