### Outcome measures

Outcome measures will be evaluated just before the start of the intervention (T0), after 4 weeks of light therapy (T4) and after 4 weeks of follow-up (T8). Changes in outcome measures (T0 – T4, T4 – T8, or T0 – T8) will be compared between the two study conditions. Additionally, several outcome measures will also be evaluated weekly during the intervention period (T0, T1, T2, T3, T4, T8) to allow for analysis or temporal changes in these measures. A schematic overview of the outcome measures is depicted in Table 1.

**Table 1 Tab1:** Outcome measures

Weeks relative to start intervention (T)			0	1	2	3	4	5	6	7	8
Visits		S	1				2				3
Telephone contact				1	2	3			4		
Run-in phase		X-es	X-es								
Intervention phase				X-es	X-es	X-es	X-es				
Follow-up phase								X-es	X-es	X-es	X-es
Participant characteristics	Psychiatric diagnosis, seasonality, chronotype, sleep apnoea, medical history, current medication, biochemical blood tests, sociodemographic factors	X	X								
Psychometrical measures	Depressive symptoms		X	X	X	X	X				X
	Anxiety symptoms		X	X	X	X	X				X
	Diabetes-related distress		X				X				X
	Quality of life, disability		X				X				X
Glucometabolic measures	Insulin sensitivity		X				X				
	HbA1c level		X				X				X
	Fasting glucose level		X				X				X
	Hypoglycaemic events		X	X	X	X	X				X
Circadian mediating factors	Diurnal HPA axis activity		X				X				X
	Objective sleep		X				X				X
	Subjective sleep		X	X	X	X	X				X
Other factors	Body weight, body mass index, waist-hip ratio, body composition		X				X				X
	Physical activity		X				X				X
	Autonomic nervous system function		X				X				X
Safety	Adverse effects		X	X	X	X	X				X
	Ophthalmological examination	X									X
Compliance	Participant-report compliance			X	X	X	X				
	Light meter		X				X				X

*Abbreviations*: *S* screening, *HPA* hypothalamic-pituitary-adrenal

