#### Primary outcome measures

Depressive symptoms will be assessed by the self-report version of the Inventory of Depressive Symptomatology (IDS) (T0, T1, T2, T3, T4, T8) [57]. The IDS allows for profiling of depression, as the questionnaire discriminates directions of the weight, appetite, sleep and psychomotor symptoms, and can be used to determine depression severity. Scores between 14 and 25 indicate mild depression; scores between 26 and 38 indicate moderate depression; scores between 39 and 48 indicate moderate to severe depression; and scores of 49 and greater indicate severe depression. A reduction of 50 % or greater of the baseline depression score is regarded as a clinically significant reduction in depressive symptoms. Depression remission is *a priori* defined as an IDS score of 13 or less.

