### Statistical analyses

Data will be analysed using SPSS (version to be determined). Participant and baseline characteristics across treatment groups will be compared using analysis of variance (ANOVA) and chi-squared statistics. Analyses of our primary outcome measures will be performed on the basis of intention to treat. The superiority of the bright white-yellowish light condition compared to dim green light condition will be tested using a repeated measures mixed models design. Both treatment (independent of time) and condition*time interaction effects will be evaluated. Repeated measures logistic regression will be applied to test differences in depression remission rates. Preacher and Hayes mediation analysis will be performed to test whether the effects of light therapy are mediated by restoration of the circadian rhythmicity. Post hoc analyses of this study may include subgroup or discriminant analysis to test if participant characteristics can be identified that predict positive effects of light therapy, such as baseline depression severity, baseline depressive symptoms profile, baseline insulin sensitivity, baseline HbA1c, chronotype, or baseline insomnia severity, seasonality of depression and time of year at which the participant was included in the study.

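### Remission is defined as an IDS of 13 or less with no condition on the T0 score, so a participant already at 13 or less before treatment who stays there counts as a remitter

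*Protocol article*

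**What the plan says.** **Entry.** Under Participants: "Eligibility for participation will be determined during a screening visit, which constitutes a standardised psychiatric interview". The depression criterion under Inclusion criteria is "having a major depressive episode according to DSM-IV criteria". Neither the inclusion nor the exclusion criteria set a minimum IDS score.

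**Interval before treatment.** The Design section describes the trial as "consisting of a run-in period of at least 1 week to allow for study effects", followed by four weeks of intervention and four of follow-up. Table 1 places the run-in between screening and week 0. No upper limit on its length is given, and no second look at depression status before treatment is described.

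**Baseline.** The Outcome measures section and Table 1 put the first IDS at T0, immediately before treatment, with repeats at T1 to T4 and at T8. Changes are counted from T0.

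**Remission.** Under Primary outcome measures, remission is fixed in advance and "defined as an IDS score of 13 or less". The same paragraph starts the mild depression band at 14. Under Statistical analyses: "Repeated measures logistic regression will be applied to test differences in depression remission rates".

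**The concern.** Entry and remission rest on different instruments at different times. Entry needs a DSM-IV episode at interview. Remission needs a low self-rated score later. Nothing in the definition requires the participant to have been above the cut-off when treatment began.

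Someone who meets DSM-IV criteria at screening, scores 12 at T0 and stays near 12 satisfies the remission definition at every assessment, including the one before treatment. This can plausibly happen: there is no severity floor at entry, an open-ended interval separates the interview from the first IDS, and the mild band begins directly above the remission cut-off.

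At stake is the meaning and the power of the remission comparison. Participants who could not remit are added to the numerator in both arms, which raises the reported rates and shrinks the contrast. If the matter is left until results are seen, the choice to keep or exclude these participants becomes post hoc.

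**Working it through.** **The plan's own figure.** The only related number is the sample size for IDS scores. With d = 0.50, two-sided α of 0.05 and power of 0.80, an unadjusted comparison needs 63 per arm. Adjusting for baseline with the stated correlation of 0.6 gives 62.8 × (1 − 0.36) = 40.2, and exact power at 42 per arm is 0.81. For attrition, 84 / 0.85 = 98.8, against the stated 98. The plan's figure is reproduced closely enough and is not in question here. It does not address remission, and the document gives no remission rates.

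**Step 1: how many could be at 13 or less at T0?** Assume a normal T0 IDS. The share is Φ((13.5 − mean) / SD).
- Mean 34, SD 9: Φ(−2.28) = 0.011, about 1 of 98.
- Mean 30, SD 11: Φ(−1.50) = 0.067, about 6 to 7 of 98.
- Mean 26, SD 13: Φ(−0.96) = 0.168, about 16 of 98.

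The means and SDs are assumptions. Over means of 26 to 34 and SDs of 9 to 13, the share runs from 1% to 17%.

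**Step 2: effect on the difference.** Let q be the share at 13 or less at T0, s the proportion of them still there at the later assessment (taken as equal in both arms), and p the remission rate among the others. The observed rate in an arm is q·s + (1 − q)·p. In the difference between arms, s cancels:

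observed difference = (1 − q) × true difference.

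A true difference of 25 points becomes 0.95 × 25 = 23.75 at q = 5% and 0.90 × 25 = 22.5 at q = 10%, whatever s is.

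**Step 3: effect on rates, odds ratio and power.** Assume p = 40% v 15% and s = 90%. Power uses the normal approximation for two proportions at one assessment, two-sided α of 0.05, with 42 per arm. The last column drops the share q and uses 42 × (1 − q) per arm with 40% v 15%.

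| q | Observed rates | Difference (points) | Odds ratio | Power as written | Power restricted |
|---|---|---|---|---|---|
| 0% | 40.0% v 15.0% | 25.0 | 3.78 | 0.74 | 0.74 |
| 5% | 42.5% v 18.8% | 23.75 | 3.20 | 0.66 | 0.71 |
| 10% | 45.0% v 22.5% | 22.5 | 2.82 | 0.59 | 0.69 |
| 20% | 50.0% v 30.0% | 20.0 | 2.33 | 0.46 | 0.64 |

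The q = 10% row in full:
- As written, the pooled rate is 0.3375. The null standard error is √(2 × 0.3375 × 0.6625 / 42) = 0.1032, and the alternative is √((0.45 × 0.55 + 0.225 × 0.775) / 42) = 0.1002. Power is Φ((0.225 − 1.96 × 0.1032) / 0.1002) = 0.59.
- Restricted to about 38 per arm, the pooled rate is 0.275 and the standard errors are 0.1024 and 0.0983. Power is Φ((0.25 − 1.96 × 0.1024) / 0.0983) = 0.69.

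**Step 4: other assumed rates.** With 45% v 20%, s = 85% and q = 10%, the observed rates are 0.9 × 0.45 + 0.1 × 0.85 = 49.0% and 0.9 × 0.20 + 0.1 × 0.85 = 26.5%. The difference is again 22.5 points, and the odds ratio falls from 3.27 to 2.66.

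**The case against.** **The effect is limited.** The main IDS analysis is a mixed model on scores, which the cut-off does not touch. Randomisation balances low T0 scores in expectation, so the harm is dilution, not a false claim of superiority. Every input to the size is assumed. All of this stands and limits the weight of the point.

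**The handling of T0 in a logistic model belongs in a SAP.** This is true of how T0 enters the model, and that is not criticised here. The definition itself, however, is stated in the article, is declared in advance, and is tied to a named test. Read as written, it labels people as remitters who were never above the cut-off at baseline.

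**Stronger readings that the document does not support.**
- A reader might infer that the run-in does nothing for the IDS because the questionnaire is first given at T0. That does not follow. Keeping early study effects out of the result requires a baseline taken after the run-in, and T0 is exactly that. Improvement between screening and T0 lies outside the change from T0.
- A reader might add that a drop on first completing the IDS then falls within treatment, so that a screening IDS is needed. The document mentions no such drop. If there is one, it is common to both arms and does not bias their comparison. A screening IDS would be a gain in precision, not the correction of an error.
- A reader might want the 50% reduction criterion restricted in the same way. That criterion is relative to each participant's own T0 score, so a low T0 score does not in itself make anyone a responder.

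**Conclusion.** The point holds for the remission definition only. With eligibility set at interview before the run-in, no IDS minimum and no T0 condition on remission, a participant at 13 or less at T0 who stays there is counted as a remitter. Remission rates in both arms are inflated, and the difference shrinks by the factor (1 − q).

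A 5% to 10% share costs about 1 to 2.5 points of an assumed 25-point difference. Under the 40% v 15% assumption, power at one assessment falls from 0.74 to between 0.66 and 0.59. These figures rest on assumed T0 distributions and remission rates, and on equal persistence in both arms. If very few participants score 13 or less at T0, the effect is negligible.

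The point worsens with the share at 13 or less, is cheap to settle now, and is best settled before unblinding. It casts no doubt on the run-in, the IDS schedule or the stated sample size.

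**What to change.** Add one sentence to the remission definition: remission is analysed at the assessments after T0 among participants with a T0 IDS of 14 or more, the protocol's own lower bound for mild depression. Report by arm the number at 13 or less at T0, and repeat the analysis in all randomised participants as a sensitivity analysis.

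T0 precedes treatment, so the subset is not defined by anything that treatment could have changed, and the arms remain comparable as randomised. No new data are needed and enrolment does not change, so the rule can apply to participants already recruited.

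The cost is a slightly smaller denominator: at a 10% share, about 38 instead of 42 per arm. On the assumed inputs the clearer contrast more than repays this, with power of 0.69 instead of 0.59. The remission result would then describe participants above the cut-off at baseline, which the report should say.

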**Fig. 2 Fig2:**
[figure not shown]
Study protocol. Schematic overview of the study protocol. *Abbreviations*: *S* screening, *T0* start of the intervention, *T4* 4 weeks relative to the start of the intervention, *T8* 8 weeks relative to the start of the intervention

### Approval

This study will be executed in accordance with the Helsinki Declaration [41]. Participation in the study is voluntary and written informed consent is obtained. Participants can withdraw their consent to participation at any time, without specification of reasons. The ethical committee of the VU University Medical Centre, Amsterdam, The Netherlands, approved this study.

### Participants

Participants will be recruited using a number of strategies: (1) Participants of previous research studies of the VU University Medical Centre will be informed about the study; (2) patients will be informed about the study by affiliated health-care-workers; (3) advertisements in local newspapers, folders and posters in waiting rooms of affiliated health-care-institutions; and (4) via our website. In case patients are interested in participation, a screening consisting of three questions will be applied by telephone. Only patients without a history of laser photocoagulation for the treatment of diabetic retinopathy and scoring 2 or more on one or both questions of the Patient Health Questionnaire-2, a screening tool for a major depressive episode [42], will be invited for a screening visit.

Eligibility for participation will be determined during a screening visit, which constitutes a standardised psychiatric interview, as assessed with the Composite International Diagnostic Interview (CIDI) WHO version 2.1 [43], a medical interview on disease history and medication, physical and blood examination, visual acuity test and fundus photography.

